### **C. Rationale**

1. There is considerable evidence that physiological function in pwMS can be improved with targeted exercise interventions. The general benefit of exercise in pwMS, highlights the possibility that a well-designed program will reduce frailty in this population. Our recently completed RCT consisting of a motor-cognitive rehabilitation intervention was successful in reducing hallmarks of frailty in pwMS. The promise shown by our program in enhancing several key moderators of frailty, seems to open the possibility that adding elements targeting frailty such as an evidence-based resistance training component will have a greater effect on reducing frailty in pwMS.
2. The main limitation of the current body of knowledge is the lack of evidence regarding the dynamic nature (i.e., modifiability) of frailty in MS. Additionally, it is not clear whether well-designed exercise-based interventions can reduce frailty in pwMS, and whether measures of frailty, such as the frailty index, are reliable (and therefore appropriate to evaluate the effects of interventions) in pwMS. Moreover, interventions in older adults designed to target frailty have had numerous methodological limitations, namely limited assessment of frailty prior to and post-intervention and lack of control groups. The current project is designed to overcome these limitations and set the foundation for interventions to reduce frailty in MS.
3. This project aims to improve the treatment of MS. This project will help determine if well-designed exercise-based interventions can reduce frailty in pwMS, which could in turn improve the overall quality of life in pwMS.

## **II. Research Plan and Design**

**A. Study Objectives:** The broad research goal of this study is to provide novel data regarding the potential efficacy of multimodal exercise to reduce frailty in pwMS and will set the foundation for our long-term goal of identifying novel interventions to improve the quality of life of persons with MS. The specific aims of the project will be to determine the feasibility of a multimodal exercise training in pwMS (Aim 1), and to explore the effects of the multimodal exercise training on frailty in pwMS (Aim 2).

**B. Study Type and Design:** Using a pilot single-blind randomized controlled trial (RCT) study design, ambulatory individuals living with MS will be allocated to 6 weeks of multimodal exercise training (n=30) or to a waitlist control group (n=30) (Figure 1).

[figure not shown]

Figure 1. Study design.

The following outcomes will be collected to accomplish the study aims:

**Aim 1: Feasibility Outcomes:** The following outcomes, based on the guiding principles for feasibility studies, will be utilized to examine the feasibility of the Virtual Reality and Resistance Training for MS (VRRT4MS) program in the study population: a) participant recruitment, i.e., number of consented individuals/number of approached individuals (expressed as a percentage); b) retention rate, i.e., number of participants completing the intervention/number of participants enrolled at baseline (expressed as percentage); c) appropriateness of data collection and training procedures, as quantified through the percentage of missing data for analysis purposes (i.e., missing items in the frailty index) and through time spent in training, respectively; d) participant safety, i.e., number of adverse and serious adverse outcomes throughout the study and self-reported pain, assessed by the numeric pain rating scale, during each training session (the Borg and Omni scales of perceived exertion will also be administered throughout each training session to differentiate exertion from pain); e) evaluation of resources, i.e., difference between proposed and actual research timeline; f) user engagement, i.e., study participant feedback questionnaire. We note that the effects of VRRT4MS on the primary frailty outcome, namely the frailty index (AIM 2), will also represent a further feasibility outcome of the intervention.

**Aim 2: Primary Frailty Outcomes:** The primary frailty outcome of this investigation will be the frailty index. This parameter was selected based on its significant potential to quantify fine-grained changes in frailty, compared to the Fried phenotype, and on our preliminary data on frailty in MS. Notably, a recent study in hospitalized older adults has identified a change in frailty index score  $> 0.03$  as a minimum clinically important difference (MCID) in frailty status.

**Other measures:** In addition to the frailty outcomes, we will also collect sociodemographic (i.e., age, gender, body mass index, marital and occupational status) and relevant clinical measures (i.e., number of prescribed medications, disease duration, MS type) at baseline.

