**Aim 1: To determine the feasibility of a multimodal exercise training in pwMS.**

We hypothesize that at least 80% of participants will complete the multimodal exercise training and that no serious adverse events will be recorded during the training sessions. In addition to feasibility, we will also generate the effect sizes from the intervention, which will inform the development of a fully powered randomized controlled trial (RCT).

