### **C. Sample size, statistical methods, and power calculation**

1. Descriptive statistics (frequency/percent and mean/SD) will be mainly used to summarize participants' characteristics and intervention outcomes. The means and 95% CIs for pre-post changes in the primary (i.e., frailty index) outcome will be estimated. No imputation will be considered for missing data. The Wilcoxon rank sum test will be used for comparing the pre-post changes in frailty index between the two groups. The intervention will be considered feasible if the retention rate and the proportion of completed sessions are more than 80%. Pre-generated randomization codes will be prepared by the biostatistician ([name]). The randomization ratio will be 1:1.
2. [name], who will be the assessor for the study assessments, will be blinded to which group the participants have been allocated to. Participants will be aware of which group they are in. The study coordinator and [name] will have access to the code to the blind. The code will not need to be broken unless there are unforeseen circumstances in which [name] needs to know which group a particular participant was assigned to. Following the baseline assessment (visit 2), participants will be randomized to one of the two groups based on pre-generated randomization codes prepared by the biostatistician, [name]. In accordance with the CONSORT guidelines, sequence generation, allocation concealment and group allocation will be blinded and separate processes.
3. For this pilot study, we plan to enroll a convenience sample of 60 ambulatory people (30 per group) with Multiple Sclerosis living with frailty that meet inclusion/exclusion criteria. These subjects will provide feasibility data and preliminary efficacy data for designing a future study if the findings are promising. We expect a 15% dropout rate, and at that at least 24 subjects per group will complete the study.

**D. Subject Criteria (See Vulnerable Populations appendix, if applicable):** We will enroll 60 ambulatory pwMS living with frailty. During Visit 1, we will screen subjects for frailty based on established cut-offs according to the Fried phenotype. This screening tool was chosen to ensure a time- and cost-effective identification of pwMS who are frail.

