#### **E. Specific methods and techniques used throughout the study**

1. **Laboratory tests:** Participants will be asked to complete a blood draw, in fasting conditions (in the morning), during study visits 2 and 3. The blood draws will be performed by a trained nurse at the Landon Center on Aging. The blood drawn will be done to assess biomarkers that are correlates of frailty such as NfL, BDNF, GFAP, CRP, IL-6, IL-10, TNF-alpha, IFN-gamma, and CXCL9, mi-RNAs. The amount of blood drawn will be approximately 12-15 mL.
2. **Study Procedures:** Participant involvement in this study will begin with the screening visit, where subjects will be screened for eligibility using objective diagnostic criteria. The screening visit will take place at the KU Center for MS Care and will take about 10-15 minutes. At the screening visit, participants will go through the informed consent with a study team member. If the participants consent, they will then complete the Mini-Cog questionnaire and the Fried phenotype to determine if they meet the frailty criteria. The Fried phenotype evaluates 5 components: fatigue, weakness, ambulation, inactivity, and loss of weight. Fried scores range from 0-5 (i.e., 1 point for each component). Higher scores reflect higher frailty. Subjects who total at least 3 points out of 5 will be classified as frail and will be eligible to participate. The Fried phenotype will also be repeated after the intervention, during Visit 3.

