sum of all deficit-related scores divided by the sum of the total number of possible health deficits. The same procedures will be repeated during the post-intervention assessment (Visit 3). During the screening visit and visit 3, participants will complete two pain questionnaires and a pain threshold test. First, participants will complete the Paindetect, a screening tool of neuropathic pain (one of the most common pain pwMS) and the Fibromyalgia Survey Criteria (a proxy measure of nociplastic pain). Then, participants will undergo a pressure pain threshold involving the middle part of bulk of medial and lateral gastrocnemius muscles as well as the thumbnail of the participant's dominant hand. This is measured with a digital algometer, which has been shown to have good reliability in the gastrocnemius region. The digital algometer is made up of a 1-cm-wide disk located on the middle part of bulk of medial and lateral head of gastrocnemius muscles. The algometer's pressure will be increased gradually (with a speed approximately 1 N/cm^2 per second) and will be stopped immediately when the participant reports the transition from discomfort to pain. The average value of three measurements will be recorded.

**Table 1.** Synopsis of the 70-item frailty index: Domains, sources and measures utilized as health deficit items.

| Domains of frailty             | Items, number | Sources                                           | Measures                                                                                                                                                                      |
|--------------------------------|---------------|---------------------------------------------------|-------------------------------------------------------------------------------------------------------------------------------------------------------------------------------|
| Global health                  | 2             | MSQoL-54                                          | self-reported health.                                                                                                                                                         |

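### As defined, the retention rate cannot exceed 30/60 = 50% through Visit 3, so the criterion of more than 80% is out of reach; numerator and denominator should be limited to the exercise arm

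*Protocol*

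**What the plan says.** Item b of the Aim 1 feasibility outcomes (Protocol II.B) gives the formula: "retention rate, i.e., number of participants completing the intervention/number of participants enrolled at baseline (expressed as percentage"). It names neither an arm nor a time limit.

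The decision rule stands in II.C.1 and is repeated in V.B: "The intervention will be considered feasible if the retention rate and the proportion of completed sessions are more than 80" per cent. The inequality is strict, and both components must be met.

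The design in II.B has participants "allocated to 6 weeks of multimodal exercise training (n=30) or to a waitlist control group (n=30"). On timing, II.C.2 says: "Following the baseline assessment (visit 2), participants will be randomized to one of the two groups". Under II.E.2 (Control Group), the waitlist is passive for 6 weeks and its members may take up the training, if they want it, only after Visit 3.

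Two other places bear on what was meant. The Aim 1 hypothesis in I.A expects that "at least 80% of participants will complete the multimodal exercise training", and V.B repeats it. The sample-size paragraph, II.C.3, counts completers in both arms: "We expect a 15% dropout rate, and at that at least 24 subjects per group will complete the study".

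**The concern.** Feasibility is Aim 1, and retention is one of the two components of the only formal feasibility rule in the protocol. The formula divides an event that, before Visit 3, can happen only in one arm by a headcount taken before the arms exist. With 1:1 allocation this halves the result. A trial in which every trainee finished would score 50% at Visit 3 and miss a threshold of more than 80%. This is a stated rule that gives a wrong answer, so it is more than a detail awaiting a statistical analysis plan.

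Anyone analysing the trial would have to depart from the formula, and the choice of departure matters. If it is made once the counts are known, it can decide whether the retention component passes.

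**Working it through.** **Inputs from the protocol.** 60 enrolled, 30 per arm (II.B, II.C.3); randomization after Visit 2 (II.C.2); threshold strictly above 80% (II.C.1, V.B); 15% dropout and at least 24 completers per group (II.C.3); 18 training visits (II.E.2).

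**The plan's own figure.** 30 × (1 − 0.15) = 25.5 expected completers per group. The stated floor of 24 lies below this and is compatible with it. 24/30 = 80.0% corresponds to 20% dropout, so the floor is cautious and not an error.

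**Formula as written, through Visit 3.**
- Perfect adherence: 30/60 = 50.0%
- 15% dropout: 25.5/60 = 42.5%
- 24 exercise completers: 24/60 = 40.0%

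None reaches 80%.

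**Formula as written, counting later waitlist training.** More than 80% of 60 means more than 48, so at least 49. If all 30 exercise participants finish, 49 − 30 = 19 waitlist participants must opt in and finish. If 25 exercise participants finish, 49 − 25 = 24 must do so.

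**Two possible repairs.**
- Exercise-arm version: completers of training / 30. More than 80% needs at least 25 (25/30 = 83.3%; 24/30 = 80.0% fails).
- Pooled version: both arms attending Visit 3 / 60. More than 80% needs at least 49 (49/60 = 81.7%; 48/60 = 80.0% fails).

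For the counts below, exercise participants who finish training are taken to be those who reach Visit 3.

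| Exercise completers | Control completers | Exercise-arm version | Pooled version |
|---|---|---|---|
| 24 | 25 | 80.0%, fails | 49/60 = 81.7%, passes |
| 19 | 30 | 63.3%, fails | 49/60 = 81.7%, passes |
| 30 | 18 | 100%, passes | 48/60 = 80.0%, fails |

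**How often the two versions disagree.** Assume independent participants, with X ~ Bin(30, pe) finishing in the exercise arm and Y ~ Bin(30, pc) reaching Visit 3 in the control arm. The exercise-arm version passes if X ≥ 25; the pooled version passes if X + Y ≥ 49. The probabilities come from exact enumeration.

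| pe / pc | Exercise-arm passes | Pooled passes | Disagree |
|---|---|---|---|
| 0.85 / 0.85 | 71% | 82% | 21% |
| 0.90 / 0.90 | 93% | 99% | 7% |
| 0.80 / 0.90 | 43% | 82% | 41% |
| 0.75 / 0.95 | 20% | 83% | 63% |

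Only the first row follows from the protocol's 15% dropout; the others are assumed, to show the range. In the first row the 21% is made up of 15.7% where only the pooled version passes and 4.8% where only the exercise-arm version passes (20.6% before rounding).

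**The second criterion.** Suppose completed sessions are counted over 30 × 18 = 540, an assumption because the protocol does not state the denominator. More than 80% then needs more than 432 sessions.
- With 19 exercise completers at full attendance, 19 × 18 = 342 are supplied. The 11 dropouts would need more than 90 between them, above 8.2 each on average, or the joint rule fails anyway.
- With 24 completers at full attendance, 24 × 18 = 432 are supplied, and a single session from the other six is enough to pass.

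**The case against.** The best defence is that the intent is clear. Item b belongs to a list of measures of the exercise programme's feasibility, and its numerator is completion of the intervention. The Aim 1 hypothesis, "at least 80% of participants will complete the multimodal exercise training", uses the same unqualified word for participants and can only mean the exercise arm. The timeline (II.E.5) likewise ties completed training to about 30 people. This stands: the exercise arm is the likely intended denominator. It does not make the formula correct, and it is a reason to write that denominator down.

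The pooled version has weaker support. It replaces the stated event with attendance at Visit 3. Its basis is the dropout sentence in II.C.3 and visit labels in II.E.2 that apply to both arms, such as "The Fried phenotype will also be repeated after the intervention, during Visit 3". Such a label does not turn a passive control into a completer of the intervention. Pooling is therefore best seen as a repair to rule out, and not as an equal rival.

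A reader might infer two stronger things, and the protocol supports neither. One is that the rule must fail whatever the adherence. Item b has no time limit, and enough optional waitlist training after Visit 3 could lift the ratio above 80%, although that training is voluntary and no assessment after it is described. The other is that the two versions lead to opposite feasibility verdicts. The rule is joint, and every disagreement figure above concerns the retention component alone.

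It is also fair to say that this is a pilot, that the larger disagreement figures rest on assumed unequal arms, and that completers by arm are simple counts from which a reader could recompute either ratio. That limits the harm. It does not remove a faulty threshold rule.

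**Conclusion.** Wrong as written. Through Visit 3 the defined ratio is capped at 30/60 = 50% and cannot meet the criterion of more than 80%. This needs no assumption beyond the planned arm sizes. It could be met later only if at least 19 of the 30 waitlist participants finished the optional training, and that number applies when every exercise participant finishes.

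Repairing the formula by pooling would let good waitlist attendance hide poor exercise completion in this component. At the protocol's own 15% dropout in both arms, the pooled and exercise-arm versions of the component differ in about 21% of trials. That figure assumes independent participants and that exercise participants who finish training are the ones who reach Visit 3. How often the overall feasibility conclusion would change is not determined, because the completed-sessions criterion may still fail the joint rule.

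The frailty index analysis and participant safety are not affected.

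**What to change.** Amend item b in II.B so that retention, for the rule in II.C.1 and V.B, is the number randomized to exercise who complete the intervention divided by all randomized to exercise (n = 30). State that at least 25 are needed, since 24/30 = 80.0% does not exceed 80%, and report the rate with its 95% confidence interval. Report Visit 3 completion separately by arm, without a threshold, because waitlist retention also informs a future trial. State that optional waitlist training after Visit 3 does not count.

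The cost is two or three sentences, with no new data, visits or staff. The drawbacks are that the rate rests on 30 people and is imprecise (25/30 = 83.3%, exact 95% confidence interval 65.3% to 94.4%), and that waitlist retention carries no threshold.

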### **C. Sample size, statistical methods, and power calculation**

1. Descriptive statistics (frequency/percent and mean/SD) will be mainly used to summarize participants' characteristics and intervention outcomes. The means and 95% CIs for pre-post changes in the primary (i.e., frailty index) outcome will be estimated. No imputation will be considered for missing data. The Wilcoxon rank sum test will be used for comparing the pre-post changes in frailty index between the two groups. The intervention will be considered feasible if the retention rate and the proportion of completed sessions are more than 80%. Pre-generated randomization codes will be prepared by the biostatistician ([name]). The randomization ratio will be 1:1.
2. [name], who will be the assessor for the study assessments, will be blinded to which group the participants have been allocated to. Participants will be aware of which group they are in. The study coordinator and [name] will have access to the code to the blind. The code will not need to be broken unless there are unforeseen circumstances in which [name] needs to know which group a particular participant was assigned to. Following the baseline assessment (visit 2), participants will be randomized to one of the two groups based on pre-generated randomization codes prepared by the biostatistician, [name]. In accordance with the CONSORT guidelines, sequence generation, allocation concealment and group allocation will be blinded and separate processes.
3. For this pilot study, we plan to enroll a convenience sample of 60 ambulatory people (30 per group) with Multiple Sclerosis living with frailty that meet inclusion/exclusion criteria. These subjects will provide feasibility data and preliminary efficacy data for designing a future study if the findings are promising. We expect a 15% dropout rate, and at that at least 24 subjects per group will complete the study.

**D. Subject Criteria (See Vulnerable Populations appendix, if applicable):** We will enroll 60 ambulatory pwMS living with frailty. During Visit 1, we will screen subjects for frailty based on established cut-offs according to the Fried phenotype. This screening tool was chosen to ensure a time- and cost-effective identification of pwMS who are frail.

1. Inclusion criteria: Subjects must be aged 40-65 years old to be enrolled in this study. Subjects must meet 3 of 5 Fried's criteria (weight loss; fatigue; weakness; ambulation; inactivity) to be considered. Subjects must have a confirmed diagnosis of MS by the treating neurologist, be free from MS relapses in the last 30 days, have an Expanded Disability Status Scale (EDSS) score  $\leq 6.0$ , and be fluent in spoken and written English.
2. Exclusion criteria: Subjects will be excluded from participation if they are unable to walk unassisted for at least ten meters, are diagnosed with other clinically important neurological conditions (such as Parkinson's Disease, epilepsy, etc.), exhibit severe cognitive impairment (as determined by a Mini-Cog score  $<3$ ), and are diagnosed with active psychiatric problems. Additional exclusionary factors include unstable cardiovascular conditions (e.g., malignant arrhythmias, critical mitral stenosis, clinically severe left ventricular outflow obstruction, critical proximal coronary artery stenosis), arthritis of the lower limbs, acute lower back or lower limbs pain, rheumatic and/or severe orthopedic problems that may interfere with resistance training. Co-I [name]

will confer with the research team to ensure that the inclusion/exclusion criteria are adequately implemented.

3. **Withdrawal/Termination criteria:** Participants could be withdrawn from the study due to a variety of circumstances. Participants may be withdrawn if they develop a condition deemed exclusionary. Participants may be withdrawn from the study if the PI, and/or the study team deem that it is in the participant's best interest to be withdrawn, or if a significant safety concern has been identified. If there are any concerns that the participant and/or study team will be at risk if the participant continues, they will be withdrawn. Some participants initiate withdrawal based on physical health or availability, or other personal choices.
4. Subjects currently enrolled in other exercise trials will not be considered eligible to participate.

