**Aim 2: To explore the effects of the multimodal exercise training on frailty in pwMS.**

We hypothesize that participants in the multimodal exercise group will have greater reduction in frailty index than participants in the control group. Moreover, we expect that participants randomized to multimodal exercise will also exhibit a clinically meaningful change in the frailty index (i.e.,  $>0.03$ ).

**Exploratory aim: To compare pain levels in pwMS with and without frailty, as well as to explore changes in pain before and after the exercise training.**

We hypothesize that frail pwMS will have higher pain levels compared to the non-frail, and that participants randomized to the multimodal exercise training program will have a greater reduction in pain compared to participants randomized to the control group.

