## **B. Background and Significance**

1. **Study Significance:** This proposed investigation is designed to examine the feasibility of an exercise-based intervention to reduce frailty in people living with MS. The proposed research will be the first to establish the feasibility of targeting frailty in pwMS and will begin to examine the dynamic nature of frailty in MS. This project will also yield the effect sizes necessary to power a large scale RCT to reduce frailty in pwMS. These advances will pave the way for planned prospective studies toward effective targets for diagnostics, and rehabilitation of frailty in MS.
2. MS is a chronic, immune-mediated neurodegenerative disease that affects ~1 million individuals in the United States. It is characterized by demyelination and neuronal loss. MS is one of the most common causes of non-traumatic disability among adults of 20 – 40 years globally and is second only to heart failure in direct all-cause medical costs for chronic conditions. Early in the disease process there are acute episodes of neurological deficits (i.e., relapses) resulting from acute inflammatory demyelination. The location of the demyelinating lesions determines physiological system(s) affected and symptom presentation. MS is characterized by a progressive accumulation of disability, which typically manifests through walking impairment, muscle weakness, fatigue, psychological problems, and cognitive impairment. There is a critical need to identify new approaches to promote quality of life in the MS community.

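### The frailty index comparison rests on an unadjusted rank test of change, with no pre-specified between-arm estimate, although the pilot is meant to supply effect sizes

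*Protocol*

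**What the plan says.** Protocol II.C.1 and V.A carry the same two sentences on the frailty index. On estimation: "The means and 95% CIs for pre-post changes in the primary (i.e., frailty index) outcome will be estimated". On comparison: "The Wilcoxon rank sum test will be used for comparing the pre-post changes in frailty index between the two groups". No between-arm difference, interval for such a difference, or baseline covariate is named in either place.

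The purpose of the effect estimate is stated twice. I.A, Aim 1: "we will also generate the effect sizes from the intervention, which will inform the development of a fully powered randomized controlled trial". I.B.1: "This project will also yield the effect sizes necessary to power a large scale RCT to reduce frailty in pwMS".

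I.A, Aim 2 first states a between-group hypothesis (a larger reduction with exercise than in controls). It then adds: "we expect that participants randomized to multimodal exercise will also exhibit a clinically meaningful change in the frailty index", with the threshold set at more than 0.03. V.B repeats both expectations in the same order, without the number. II.B takes 0.03 from a study of hospitalized older adults.

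The sample is one of convenience, 30 per group, allocated 1:1. II.C.3 adds: "We expect a 15% dropout rate, and at that at least 24 subjects per group will complete the study".

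**The concern.** A later sample-size calculation needs a between-arm difference, a measure of its uncertainty and a standard deviation. A rank sum test, as named here, returns a p-value. In a convenience sample with no power statement, a p-value is the least informative summary of the comparison. The protocol therefore promises effect sizes without saying which contrast they measure or how they will be computed.

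Two further matters follow. First, the frailty index is scheduled at Visit 2, ahead of randomization, yet the comparison uses it only by subtraction, which is generally less precise than adjusting for it. Second, the clinical threshold is attached to change within the exercise arm. A mean change above 0.03 there could be reported as clinically meaningful even if much of it were not due to exercise.

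**Working it through.** **1. The plan's own figure.** 30 × (1 − 0.15) = 25.5 completers per arm, so at least 24 is consistent and slightly cautious. This is the only sample-size arithmetic in the protocol. No alpha, power, SD or target difference is given, so there is no power calculation to reproduce. The steps below use 24 per arm, N = 48.

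**2. What the planned summaries already give.** If the mean change and its 95% CI are reported by arm, each arm's standard error is the half-width divided by the t quantile. The unadjusted difference is the difference of the two means, with SE = √(SE₁² + SE₂²), and each change-score SD is SE × √n. If the SDs at both visits are also reported, the pre-post correlation ρ follows from SD(change)² = SD₀² + SD₁² − 2ρ·SD₀·SD₁, and from it an approximate residual SD. What is missing is a pre-specified contrast and the adjusted estimate.

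**3. Precision of adjustment against change scores.** With equal SD s at both visits:
- change score: variance proportional to 2s²(1 − ρ)
- baseline-adjusted: variance proportional to s²(1 − ρ²)
- ratio: (1 + ρ)/2

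Estimating the slope costs a factor of about 1 + 1/(N − 4) = 1 + 1/44 = 1.0227. The protocol gives no ρ, and I.B itself says the index's test-retest reliability in MS needs more research, so a range is shown.

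| ρ (assumed) | (1 + ρ)/2 | × 1.0227 | Net SE reduction | Change-score n per arm for equal precision |
|---|---|---|---|---|
| 0.3 | 0.650 | 0.665 | 18.5% | 36.1 |
| 0.5 | 0.750 | 0.767 | 12.4% | 31.3 |
| 0.7 | 0.850 | 0.869 | 6.8% | 27.6 |
| 0.8 | 0.900 | 0.920 | 4.1% | 26.1 |
| 0.9 | 0.950 | 0.972 | 1.4% | 24.7 |
| 0.95 | 0.975 | 0.997 | 0.1% | 24.1 |

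**4. The same at a difference of 0.03.** Simulation with normal data, 24 per arm, two-sided 0.05, 3,000 runs per setting and an assumed SD of 0.10:

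| ρ (assumed) | Wilcoxon on change | t-test on change | Baseline-adjusted |
|---|---|---|---|
| 0.5 | 15% | 16% | 20% |
| 0.7 | 23% | 26% | 27% |
| 0.8 | 34% | 36% | 39% |
| 0.9 | 59% | 62% | 64% |

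The total gap is about 4 to 5 points. Of that, 1 to 3 points come from ranks against a t-test under normality, not from the missing adjustment.

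**5. Why an interval is needed.** For an illustrative standardized difference of d = 0.5, SE = √(2/24 + 0.5²/(4 × 24)) = √(0.0833 + 0.0026) = 0.293, and the half-width is 1.96 × 0.293 = 0.57. The 95% CI then runs from about −0.07 to 1.07. A p-value alone hides this width.

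**6. The within-arm threshold.** II.C.2 says participants know their group. In Table 1, four domains drawn from the MSQoL-54 and MFIS questionnaires supply 2 + 6 + 5 + 6 = 19 of the 70 items. Another 6 are cognition items, mostly performance tests repeated at Visit 3. Expectation and practice can therefore move the exercise arm's own change. The waitlist arm's change removes what the arms share, such as practice; expectation tied to allocation stays in any contrast.

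**The case against.** The case for leaving the plan alone has real force. This is a pilot: Aim 1 is feasibility and Aim 2 is to explore, so power is not the criterion. A statistical analysis plan, not shown, could add the estimate and the covariate. The planned means and intervals supply most of what a later design needs (step 2). The gain from adjustment could be tiny: Table 1 has 16 comorbidity items, such as polypharmacy and fall history, that may move little in about six weeks, so a high ρ is plausible though undocumented. The between-group hypothesis comes before the 0.03 expectation, so a matching change in controls would be visible. Applying a threshold for change, taken from hospitalized older adults, to a between-arm mean difference is itself debatable.

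Most of this stands and limits the point. It does not remove it. The protocol does not leave the comparison open; it names the test twice, and it promises effect sizes without defining them.

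A reader might infer more than the documents support:
- **That no treatment effect could be obtained.** It could be, unadjusted and by hand, if the summaries are given by arm.
- **That the Wilcoxon test is biased or invalid.** Randomization makes it a valid comparison of the changes.
- **That selecting frail people makes regression to the mean a main explanation of any change.** Selection uses the Fried phenotype at Visit 1, while the analysed change is in a different instrument from Visit 2 to Visit 3. Much transient selection error would have passed before the baseline was taken.
- **That adjustment is free and its gain large.** It costs one degree of freedom, and the gain depends on an unknown ρ.

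**Conclusion.** The point holds as one of efficiency and reporting. The protocol pre-specifies no between-arm estimate with an interval for its primary frailty outcome, although such an estimate is among the pilot's stated products, and it attaches 0.03 to one arm's change. The precision forgone ranges from a useful 12% of the standard error at ρ = 0.5 to practically nothing at ρ = 0.95. It rests on equal SDs at the two visits, a linear relation and 24 completers per arm. The simulated power figures also assume normal data and an SD of 0.10; skewed or bounded data were not tried. The case for a pre-specified interval does not depend on ρ. This is a cheap improvement to make, not a threat to the trial's validity.

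**What to change.** In II.C.1 and V.A:
- Make the Aim 2 analysis a linear model of the Visit 3 frailty index on arm and Visit 2 frailty index, in all randomized participants with a Visit 3 value, analysed as allocated.
- Report the adjusted between-arm difference with its 95% CI, and the residual SD.
- Interpret 0.03 alongside that difference, not from the exercise arm's change alone, and make the matching edit in Aim 2 and V.B.
- Keep the Wilcoxon test on change as a sensitivity analysis.

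Cost: a few sentences and no new data collection. The model spends one degree of freedom and adds a mild assumption of linearity, which the retained rank test helps to check. One detail to settle: six index items come from a sensor handed out at the end of Visit 2 and worn for three days, so the text should say whether randomization waits for them. Only then is the whole baseline index a pre-randomization covariate.
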